**Figure 4 F4:**
[figure not shown]
Follow-up flow diagram in CHCN-BTH.

### Statistical Plan

All potential risk factors and outcomes will be described at baseline and at each follow-up. Normally distributed continuous variables will be summarized by the mean and standard deviation, and skewed distributed continuous variables will be described by the median and interquartile range. To compare possible differences between two groups, an independent-samples *t*-test will be used for qualitative variables with a normal or skewed distribution, and the χ^2^-test will be used for categorical variables. The χ^2^-test will be used for categorical variables in the description of the profiles of the responders and non-responders. When comparing differences among more than two groups, the Kruskal–Wallis test will be used for continuous variables, and one-way analysis of variance will be used for quantitative variables. Trajectory analysis will be used to explore the effect of risk factor changes on NCDs.

Generalized additive mixed models will be used to examine the associations of long-term air pollutant exposures with physiological indicators and the prevalence of NCDs. The exposure assessment during the follow-up period will use a time-spatial continuous prediction model. Time-dependent Cox proportional hazards models will be used to analyze the associations of air pollutant exposures with the incidence of NCDs. A penalized cubic regression spline of air pollutants will be included in the models to explore the non-linear exposure–response relationships.

To screen for biomarkers and genetic markers of NCDs, lasso regressions will be used first, and then mixed models will be used to demonstrate their effect size in the longitudinal data. Logistic regressions and generalized linear models will also be used to confirm the effect of potential risk factors on NCDs. To demonstrate a genetic susceptibility to NCDs, single-nucleotide polymorphism (SNP), lncRNA, and mRNA expression profiles will be detected using a microarray. SNPs associated with diseases will be explored by logistic regression, and haplotypes will be identified by using Plink software. Gene–gene and gene–environment interactions will be demonstrated by using generalized multifactor dimensionality reduction and the random forest (RF) method. Differentially expressed genes (DEGs) will be identified using the R software Limma package (29). The lncRNA–mRNA coexpression network will be constructed based on the expression level of DEGs using weighted gene coexpression network analysis (30, 31). MiRNAs targeted by both lncRNAs and mRNAs in the lncRNA–mRNA coexpression network will be predicted by miRDB, TarBase, and TargetScan. All of the ceRNA loops will be combined and transformed into an “lncRNA–miRNA–mRNA” ceRNA network using Cytoscape software (32).

To construct risk prediction models, lasso regression, smoothly clipped absolute deviation, RF, support vector machine, and decision tree will first be used to screen for predictors of NCDs. Then, predictors selected by machine learning methods will be used to construct different prediction models by the Cox regression model. The Cox regression model with the best discrimination and calibration will be selected as the risk prediction model.

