### Study Design and Settings

The CoHort study on CHronic disease of Community Natural population in Beijing–Tianjin–Hebei region (CHCN-BTH) is a population-based prospective cohort study, which has been registered with the Chinese Clinical Trial Registry (ChiCTR1900024725).

The sample size was estimated using the Cox regression module in PASS-NCSS 11.0 software. The parameters are as follows: statistical power is 80%, significance level is 0.05, and the lowest event rate is 50 per 100,000 (cardiovascular morbidity is ~650 per 100,000, and mortality is ~250 per 100,000; lung cancer morbidity is ~70 per 100,000, and mortality is 50 per 100,000). The log hazard ratio (HR) of PM_2.5_ per 10 μg/m^3^ is ~0.25 (HR = 1.28), the standard deviation of PM_2.5_ (per 10 μg/m^3^) is 1.4, and the *R*^2^ of PM_2.5_ with other covariates was set to 0.2. The lowest sample size was 32,037 according to the calculation of PASS software. Thus, the cohort was designed to recruit 36,000 individuals living in Beijing, Tianjin, and Hebei provinces by expecting a 10% loss to follow-up. The survey sites are shown in Figure 1. The CTCH-BTH cohort will include 30,000 community-lived individuals and 6,000 participants who undergo routine physical examinations. Most of the participants in the baseline survey were of the Chinese Han population, and ~10% of the participants were of Manchu ethnicity.

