### Sampling Methods

The cohort study was established with a multistage, stratified cluster sampling method. The cities are first selected according to geographical region, SES, and medical service quality. In the first stage, three cities were chosen as survey sites located in the southern, central, and northern parts of Hebei Province. Beijing and Tianjin are also designated survey sites. Among the above survey sites, the severity of air pollution and economic status are significantly different from each other, which can reflect the state of the natural population in Hebei Province. In the second stage, we selected districts from urban cities and counties from rural areas. In the next stage, communities were selected from districts in urban areas, while townships were selected from counties in rural areas. The new district called Xiong'an, which previously contained three rural counties, has now integrated into one urban city. In the final stage, residents in the selected area will be invited to participate in the study considering the demographic structure of the sixth national census. These procedures can ensure the representation of the sampling. Finally, the selected survey sites included 41 communities, 36 townships, and 7 functional units in five cities. Details of the sampling are shown in Figure 2.

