Indoor pollutant exposures will also be obtained from face-to-face interviews, including asking about passive smoking, cooking fuel, cooking habits, and winter heating fuel. Ambient air pollutants are generally estimated by the following procedure: (1) annual concentrations of particles with aerodynamic diameters of no >2.5 μm (PM_2.5_) will be estimated with a machine learning method at a resolution of 0.1° × 0.1° using high-dimensional expansion of numerous predictors (including ground-monitored PM_2.5_ data, satellite-derived aerosol optical depth and other satellite covariates, meteorological variables, and chemical transport model simulations). (2) Concentrations of particles with aerodynamic diameters of no >10 μm (PM_10_), nitrogen dioxide (NO_2_), SO_2_, CO, and O_3_ will be collected using air monitoring stations. In each of the study districts, there will be more than one air monitoring station. Continuous hourly concentrations will be gathered. The daily average concentrations of PM_2.5_, PM_10_, SO_2_, NO_2_, and CO at each station will be used only if >20 of the 24-hourly measurements are available. For O_3_, at least six hourly concentrations of O_3_ per day will be needed to calculate the 8-h average concentration of O_3_. The air pollutant concentration measurements are valid and are conducted in accordance with the China Ambient Air Quality Standards (GB 3095-2012). Information on outdoor activity, window opening frequency, and protective measurements during smog are also included in the questionnaire to evaluate the effect of ambient air pollutants more accurately.

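### The Cox incidence models are named without a site-level clustering term although PM2.5 is nearly shared within each of 84 sampled sites, so default-variance intervals would be too narrow for common outcomes

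*Protocol article*

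**What the plan says.** Sampling Methods describes a multistage, stratified cluster design and gives its end point: "Finally, the selected survey sites included 41 communities, 36 townships, and 7 functional units in five cities". That is 41 + 36 + 7 = 84 sites.

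Measurements states that annual PM2.5 will come from a "machine learning method at a resolution of 0.1° × 0.1" degrees. The other pollutants come from monitoring stations in the study districts. The Introduction presents the pollution contrast as geographical: differences between areas supply the exposure groups.

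The Statistical Plan covers incident disease in one sentence: "Time-dependent Cox proportional hazards models will be used to analyze the associations of air pollutant exposures with the incidence of NCDs". A penalized spline of the pollutant is added for the exposure–response curve. No frailty, cluster-robust variance or stratification by site is mentioned. The same paragraph uses generalized additive mixed models for physiological indicators and prevalence, without naming the grouping level of the random effects.

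Study Design and Settings sizes the study as follows: "The sample size was estimated using the Cox regression module in PASS-NCSS 11.0 software", with "statistical power is 80%, significance level is 0.05, and the lowest event rate is 50 per 100,000", a log hazard ratio of about 0.25 per 10 μg/m³, "the standard deviation of PM_2.5_ (per 10 μg/m^3^) is 1.4" and an R² of 0.2 with other covariates. The result is 32,037, raised to 36,000 for 10% loss to follow-up. No intraclass correlation or design effect is given.

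**The concern.** When an exposure hardly varies within a site, the information about its effect comes mainly from comparing sites. Sites also differ in disease rates for reasons the covariates will not fully capture. The default Cox variance does not see this extra variation. It counts each participant as a separate piece of evidence about the pollutant effect.

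The consequence is false precision: standard errors too small, p-values too low, and spline bands too tight. The last matters because the dose–response relation with long-term pollution is one of the article's stated reasons for the cohort. The problem grows with the number of events per site, so it is largest for common outcomes and small for rare ones.

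**Working it through.** **1. Reproduce the stated sample size.** For Cox regression with a continuous covariate and independent individuals:

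N = (z₀.₉₇₅ + z₀.₈₀)² / [P × (1 − R²) × SD² × B²]

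Inputs from Study Design and Settings: B = 0.25, SD = 1.4, R² = 0.2, power 80%, alpha 0.05 (taken as two-sided). With P = 0.0025:

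N = 7.8489 / (0.0025 × 0.8 × 1.96 × 0.0625) = 7.8489 / 0.000245 = 32,036.2, rounded up to **32,037**.

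This matches exactly with no design effect. The only inflation is for loss to follow-up: 32,037 / 0.9 = 35,597, rounded to 36,000. P = 0.0025 is 50 per 100,000 accumulated over 5 years, or the listed cardiovascular rate ("mortality is ~250 per 100,000"); the article does not say which. P = 0.0005 taken literally gives 160,182.

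**2. People per site.** 36,000 / 84 = 428.6.

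**3. Design effect.** Take exposure as constant within site, and let k be the residual coefficient of variation of rates between sites. For a rate model such as Cox:

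DE ≈ 1 + k² × (events per site)

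Standard errors are then too small by √DE, and the true type I error at nominal 5% is 2 × [1 − Φ(1.96/√DE)]. The documents do not give k. I assume 0.25, range 0.15 to 0.35.

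**4. Results.** The cardiovascular morbidity of 650 per 100,000 is read as annual. The horizons are assumptions: 5 years matches the P that reproduces 32,037 from 50 per 100,000, and 10 years matches five two-yearly follow-up rounds.

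| Outcome | P | Events per site | DE at k = 0.25 (0.15 to 0.35) | Type I error |
|---|---|---|---|---|
| Sizing outcome | 0.0025 | 1.07 | 1.07 (1.02 to 1.13) | 6% (5 to 7%) |
| Cardiovascular, 5 years | 0.0325 | 13.9 | 1.87 (1.31 to 2.71) | 15% (9 to 23%) |
| Cardiovascular, 10 years | 0.065 | 27.9 | 2.74 (1.63 to 4.41) | 24% (12 to 35%) |

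Example for the second row: 1 + 0.0625 × 13.93 = 1.87; √1.87 = 1.37; 1.96 / 1.37 = 1.43; two-sided tail 15%.

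**5. Check by simulation.** This used 84 sites of 381 people (32,037 / 84), gamma site frailty, a site-constant exposure, and a Poisson model as the rare-event equivalent of Cox. At P = 0.0325 and k = 0.2, 0.3 and 0.5, naive 95% intervals covered 87%, 79% and 63%, and type I error was 12%, 18% and 33%. The formula at 381 per site gives 11%, 18% and 33%. At P = 0.0025 coverage was 94%, 94% and 92%.

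**6. Effect on the sample size.** At P = 0.0025 and DE = 1.07, power at 32,037 falls from 80% to about 77% (79% at k = 0.15, 75% at k = 0.35). For 5-year cardiovascular morbidity, power stays above 99% after the design effect, even at k = 0.5. The harm there is overstated precision, not lost power.

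**The case against.** The strongest objection is that the Statistical Plan is silent on the variance estimator. It is part of a condensed article, and a frailty or robust variance may be in a fuller plan. This stands as far as it goes. A reader might infer that the authors have decided to treat participants as independent in the Cox models; the document does not say so. The conclusion is therefore conditional on the models being fitted as named, with the default variance. The sample-size calculation is different: there independence is shown by the exact reproduction.

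A reader might also infer that, because mixed models are used for prevalence and physiological indicators, site clustering was handled there and dropped for incidence. That is not supported. Physiological indicators are measured repeatedly, so the random effects may be for persons.

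On size, several points stand:
- The binomial form 1 + (m − 1)ρ gives somewhat larger values than the rate form used here (2.86 against 2.74 at 10 years and k = 0.25).
- k must be variation left after adjustment for covariates, and the excess scales with k².
- Exposure is not strictly fixed within a site. It changes over time, home addresses are collected, and members of a functional unit need not live near one another, so the full design effect is an upper bound for them.

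In the other direction, adjacent sites may share a grid cell and pollution may vary mainly between cities. The number of effective exposure units could then be below 84.

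A further tempting reading is that the cohort is badly undersized. The figures do not support it: the design effect for the sizing outcome is close to 1.

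**Conclusion.** The point holds in conditional form. The cluster sample, the area-assigned exposure and the independence-based sample size are all established from the article. If the Cox models are run as written with the default variance, intervals and spline bands for pollutant effects will be too narrow for common outcomes.

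For cardiovascular morbidity, standard errors would be too small by a factor of about 1.4 over 5 years and 1.7 over 10 years. These sizes rest on k = 0.25, equal sites of 429 people, exposure constant within site, and an annual reading of the stated rate. None of these is given in the documents, so they show the likely scale only. The consequence for the sample size is minor. The variance can be corrected at analysis without changing recruitment or data collection.

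**What to change.** In the Statistical Plan, specify for the time-dependent Cox models a shared frailty for community, township or functional unit, or a sandwich variance clustered on that unit. Make this the primary inference, including for the spline bands. Add a check at a higher level (district or city), because exposure may be correlated across sites; with only five cities, a city-level sandwich variance would itself be unreliable and should be read as a check only.

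In Study Design and Settings, state that 32,037 assumes independent individuals. Give the design effect under a stated between-site variation, and say which event probability and period were used.

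The cost is a few sentences and a standard software option. The downside is wider intervals. Splitting the pollutant effect into between-city and within-city parts is a reasonable optional sensitivity analysis, but it addresses confounding by city, not the standard errors.

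### Interactions are assigned to GMDR and random forest with no test of departure from main effects, so a main effect alone can be reported as an interaction

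*Protocol article*

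**What the plan says.** The genetic part of the Statistical Plan gives interaction one sentence: "Gene–gene and gene–environment interactions will be demonstrated by using generalized multifactor dimensionality reduction and the random forest (RF) method".

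The same section assigns regression to other tasks. For single variants: "SNPs associated with diseases will be explored by logistic regression, and haplotypes will be identified by using Plink software". For risk factors: "Logistic regressions and generalized linear models will also be used to confirm the effect of potential risk factors on NCDs". Neither sentence mentions interaction. The section names no product term, no comparison with a main-effects model and no main-effect adjustment of the GMDR score.

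For prediction models, the next paragraph of the plan does set out two steps: machine-learning methods screen the predictors, and Cox regression then builds the model. Interaction has no matching second step.

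Elsewhere, Study Design and Settings sizes the cohort on an exposure main effect: "The log hazard ratio (HR) of PM_2.5_ per 10 μg/m^3^ is ~0.25 (HR = 1.28"), with "the standard deviation of PM_2.5_ (per 10 μg/m^3^) is 1.4".

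**The concern.** A claim of interaction says that two factors act together in a way their separate effects do not explain. Its null hypothesis is both main effects and no interaction.

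GMDR pools the cells of a factor combination into high and low risk and asks whether that split predicts disease. Its usual test permutes the outcome scores, which removes every association. Rejection then shows only that at least one factor in the combination matters. Random forest importance likewise rises with main effects as well as interactions, so two factors with purely additive effects can both rank high.

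The second objective of the study is etiology, with environmental and genetic factors considered together, and the Abstract looks ahead to personalized prevention. A SNP of no effect that is labelled as modifying the harm of an exposure would mislead on both.

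**Working it through.** **Inputs from the article (Study Design and Settings).** Log hazard ratio 0.25 per 10 μg/m³ of PM2.5; SD 1.4 in the same units; R² with covariates 0.2; 80% power; significance level 0.05; minimum sample size 32,037.

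**The article's own figure.** It gives no figure for interaction. Its one design figure rests on the PM2.5 main effect. Events needed, two-sided:

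D = (1.960 + 0.842)² / (1.4² × 0.25² × (1 − 0.2)) = 7.849 / 0.098 = 80.09.

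80.09 / 0.0025 = 32,036.2, which rounds up to 32,037. At the stated lowest rate of 50 per 100,000 the result would be 160,182. That mismatch is a separate matter and nothing below depends on it. What matters here is that the design presupposes a PM2.5 main effect of this size.

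**Effect after a median split.** For a normal exposure, the difference between the mean of the upper half and that of the lower half is 2 × √(2/π) SDs. The log ratio is 0.25 × 1.4 × 2 × √(2/π) = 0.559, a ratio of about 1.75.

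**Why the default test rejects.** With half the population exposed and a rare disease, the exposed share of cases is 1.75 / 2.75 = 0.636, against 0.5 in controls. A rule that uses the exposure alone has balanced accuracy (0.636 + 0.5) / 2 = 0.568. Adding a SNP of no effect leaves the true value at 0.568, while the permutation null is centred at 0.5. The two-factor model therefore looks significant without any interaction. For an odds ratio of 1.3 the same steps give 1.3 / 2.3 = 0.565 and a balanced accuracy of 0.533.

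**Simulation A: one exposure and one SNP, 1:1 case-control, no interaction.** Assumed: minor allele frequency 0.3, binary exposure (50%), GMDR score equal to outcome minus its mean, nominal level 0.05. The main codings used 10-fold cross-validation, 99 permutations and 200 data sets per setting. Ranges span separately coded repeats (three for the first row, two for the second and third).

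| True model | 250 cases | 500 cases | 1,000 cases |
|---|---|---|---|
| Exposure ratio 1.75, SNP no effect | 60–69% | 87–93% | 99.5–100% |
| The same, plus SNP odds ratio 1.2 | 55–64.5% | 91–93% | 100% |
| Exposure odds ratio 1.3, SNP no effect | 14–15% | 24.5–32% | 56–63% |

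With no effects at all, GMDR rejected in 4–7%, so it is valid for its own null. The product-term likelihood-ratio test rejected in 4–5%.

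**Simulation B: search over pairs.** Assumed: n = 3,000, outcome prevalence about 20%, PM2.5 in tertiles with logit slope 0.25 and SD 1.4, eight SNPs of no effect, 5-fold cross-validation, 60 data sets.

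| Rule for declaring the best two-factor model | False interaction rate |
|---|---|
| Permutation test alone | 95% |
| Also beats the one-factor model on testing accuracy | 58% |
| Also has cross-validation consistency no lower than the one-factor model | 8% |
| Permutation test on scores adjusted for the PM2.5 main effect | 2% |

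Under the first rule the chosen pair contained PM2.5 in every data set. The logistic product term rejected in 6% of 300 data sets.

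**Safeguards in setting A.** Requiring the two-factor model to beat the one-factor model cut the rate to about 5–13%. Scores that include the main effects, with null data drawn from the fitted main-effects model (500 cases, 150 data sets), gave 2–4%.

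Random forest was not simulated.

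**The case against.** The sentence fixes two method names and nothing else: no permutation scheme, score model, covariates or rule for choosing the model order. A journal article commonly leaves such settings to the full protocol or analysis plan. GMDR with main effects in its score would satisfy the sentence and would not make the error. The article also uses its verb for showing things loosely, so the sentence need not mean a formal test.

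Much of this stands. A reader might infer that the plan, followed as written, will report main effects as interactions. The documents do not support that: the rate ran from 2% to 95% in Simulation B alone, depending on settings the article does not give. A reader might also infer that both methods test a null of no association. That describes GMDR's usual test. Random forest has no single formal null, and only the weaker statement about importance holds. PM2.5 is not named in the sentence either. It is an example drawn from the sample-size section, and air-pollutant effects are otherwise assigned to mixed and Cox models.

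What the objection does not answer is the pairing of claim and method. The article assigns interaction to these two methods, limits logistic regression to other tasks, and gives a regression step after screening for prediction but not here. That goes beyond a missing detail.

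**Conclusion.** The point holds in this form: the methods named for interaction do not, in their usual use, test departure from main effects, and no other test is named. A main effect alone can therefore be reported as an interaction.

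With unadjusted GMDR the false interaction rate was about 60–100% for the article's PM2.5 effect and 14–63% for an odds ratio of 1.3, against a nominal 5%. With the safeguards tried it was 2–58%. The effect size comes from the article. Case numbers, allele frequency, sampling scheme, outcome prevalence and the categories of PM2.5 are assumptions. No rate is given for random forest.

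The point does not touch the sample size or the models planned for air-pollutant associations. The etiology objective also rests on those models, so it would be too much to conclude that the objective as a whole fails.

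**What to change.** State that GMDR and random forest only nominate factor combinations. Base every interaction claim on a likelihood-ratio test of the product term in a logistic or Cox model that contains both main effects and the covariates, with multiplicity control over all combinations tested.

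If GMDR is to remain a test, compute its scores from a null model that includes the main effects of the factors under test, and draw the null data from that fitted model.

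The cost is plan wording and a little extra analysis, with no new data. Fewer interactions will be declared, and non-linear patterns found by GMDR will need an explicit interaction contrast. In the simulated setting with 500 cases and a true interaction odds ratio of 1.5, the product-term test had 48% power and the corrected GMDR 24%. The product term is thus the better default, though neither is strong at that size.

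### Selected predictors and biomarkers are judged with no held-out or resampled data named: p-values after selection are then invalid, and performance is optimistic mainly for rare outcomes and omics panels

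*Protocol article*

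**What the plan says.** The Statistical Plan section of the protocol article sets out two ordered procedures.

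- **Biomarkers and genetic markers.** Here "lasso regressions will be used first, and then mixed models will be used to demonstrate their effect size in the longitudinal data". The next sentence adds: "Logistic regressions and generalized linear models will also be used to confirm the effect of potential risk factors on NCDs".
- **Risk prediction.** The opening step is that "lasso regression, smoothly clipped absolute deviation, RF, support vector machine, and decision tree will first be used to screen for predictors of NCDs". The variables so retained feed several candidate Cox models, and the choice among these candidates follows a stated rule: "The Cox regression model with the best discrimination and calibration will be selected as the risk prediction model".

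The article does not say on which data discrimination and calibration are measured, or on which data the second-stage mixed models are fitted relative to the lasso. It mentions no training and test split, cross-validation, bootstrap correction, held-out site or external cohort. Later follow-up rounds (Follow-Up section) observe the same cohort members, apart from age- and sex-matched replacements for those lost, so they are not an independent sample either.

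**The concern.** Both chains select first and evaluate afterwards. A marker that survives a screen has, by construction, a large observed association in the screening data. Refitting it there with another regression family reuses the same chance fluctuation and does not test it. Likewise, several Cox models built from screened predictors and ranked on apparent performance will tend to be won by the most overfitted one.

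Biomarkers and risk prediction models are the third objective of the study, and the candidate set is wide. It covers exposures, examinations, serum markers, psychosocial data and SNP, lncRNA and mRNA arrays, and the Discussion adds proteomics and metabolomics. Some outcomes are rare. The Discussion also says that sites and participants are not randomly chosen and that risk factors vary between areas, so performance in the development data says little about another city.

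**Working it through.** **1. The plan's own figure.** None is given for prediction or biomarker work. The only computed figure is the sample size for the PM2.5 Cox regression (Study Design and Settings). With two-sided alpha 0.05 (sidedness assumed), power 80%, log HR 0.25, SD 1.4 and R² 0.2, the events needed are

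D = (1.960 + 0.842)² / [1.4² × 0.25² × (1 − 0.2)] = 7.849 / 0.098 = 80.09.

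Dividing by an event probability of 0.0025 and rounding up gives the stated 32,037. The stated lowest rate, 0.0005, would give 160,182. That mismatch is a separate matter and nothing below depends on it. The cohort was sized for one exposure, not for model development.

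**2. Expected events.** Inputs are "statistical power is 80%, significance level is 0.05, and the lowest event rate is 50 per 100,000" and "cardiovascular morbidity is ~650 per 100,000, and mortality is ~250 per 100,000", with 36,000 recruited and 10% lost, so 36,000 × 0.90 = 32,400 retained. The time unit of the rates is not stated; annual rates are assumed. Events = 32,400 × rate × years.

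| Rate per 100,000 | 2 years | 5 years | 10 years |
|---|---|---|---|
| 50 | 32 | 81 | 162 |
| 250 | 162 | 405 | 810 |
| 650 | 421 | 1,053 | 2,106 |

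Ten years corresponds to the five two-yearly rounds.

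**3. Optimism if selection data are reused.** The documents give no inputs for this, so it is an illustration under assumptions:

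- four true predictors with log odds ratio 0.25 per SD, the rest noise, 50 or 200 candidates in all;
- a univariate p<0.05 screen standing in for the machine-learning screens;
- a logistic refit on the same data standing in for Cox;
- ten controls per case;
- performance then measured in a fresh sample with 2,000 cases;
- 40 replicates at 80 and 162 events, 12 at the larger counts.

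| Events | Candidates | Apparent AUC | AUC in new data | Gap | Mean absolute coefficient of kept true predictors (truth 0.25) | Kept noise predictors with refit p<0.05 |
|---|---|---|---|---|---|---|
| 80 | 50 | 0.688 | 0.584 | 0.104 | 0.340 | 78% |
| 80 | 200 | 0.760 | 0.551 | 0.209 | 0.332 | 68% |
| 162 | 50 | 0.663 | 0.610 | 0.053 | 0.275 | 80% |
| 162 | 200 | 0.717 | 0.586 | 0.131 | 0.286 | 75% |
| 810 | 50 | 0.642 | 0.632 | 0.010 | 0.254 | 88% |
| 810 | 200 | 0.653 | 0.621 | 0.032 | 0.247 | 87% |
| 2,106 | 50 | 0.639 | 0.635 | 0.004 | 0.249 | 90% |
| 2,106 | 200 | 0.646 | 0.632 | 0.014 | 0.249 | 83% |

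**4. Reading.** The AUC gap and the coefficient inflation shrink as events accumulate. At every event count the gap is larger with 200 candidates than with 50, which is the direction that matters for omics panels. The last column does not improve with size: a valid test would show about 5% for noise predictors, and the refit shows 68 to 90%. The illustration follows one screened model and does not include the further choice among several.

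**The case against.** The strongest reply is that the article never says that all steps use the same participants. A reader might infer this from the ordered wording, but it rests on silence. Tuning, resampling and data splits are commonly left by a condensed article to a full plan, which is not shown here. Choosing the model with the best discrimination and calibration is sound if both are measured out of sample. Apparent calibration is near-perfect for any ordinary refit, so ranking on calibration makes most sense out of sample. This stands, and it is why the conclusion is conditional. It does not remove the point: the article fixes the order of steps and the selection rule, describes one data source, and leaves open the feature on which the validity of both depends.

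Other stronger readings also fail:

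- **Unpenalised Cox refits.** The text says only that Cox regression is used.
- **Confirmation of lasso-selected markers.** The sentence on confirming concerns potential risk factors in general and does not mention those markers.
- **Over-optimism everywhere.** The table shows little AUC optimism at 810 or more events, and common outcomes such as hypertension and diabetes are among those listed.
- **Dramatic null examples.** Forcing the top 10 of 500 pure-noise markers into a model (n=2,000, 10% cases) gives apparent AUC 0.67 against 0.50 in new data, with 98% of kept markers at p<0.05. Nothing in the plan forces ten markers in. A cross-validated lasso in the same setting (60 runs) kept none in 57% of runs at the minimum-error penalty, and none in any run under the one-standard-error rule.

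**Conclusion.** The concern holds in conditional form. The plan fixes a rule that keeps the best model, and a second-stage estimate for screened markers, without naming independent or resampled data for either. If the data used for selection also supply performance and effects:

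- p-values after selection are invalid at any cohort size;
- AUC is too high by about 0.05 to 0.2 at 80 to 162 events, and by only about 0.00 to 0.03 at 810 or more;
- coefficients of true predictors rise from 0.25 to about 0.33–0.34 at 80 events and about 0.28–0.29 at 162, and are close to 0.25 from 810 events on.

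The sizes rest on the assumed annual rates, 32,400 retained participants and the simulation inputs above. With few replicates they should be read as approximate. Panels with far more than 200 candidates were not simulated. The trend from 50 to 200 indicates larger optimism there at a given event count.

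**What to change.** **Prediction models.** State that the entire procedure, meaning all five screens, their tuning and the Cox refits, is repeated inside each bootstrap or cross-validation resample. Choose the final model on out-of-sample C-index and calibration. Report optimism-corrected performance together with leave-one-city-out performance across the five cities, and fix in advance the city to which Xiong'an belongs. For the rarest outcome the city-level results will be imprecise (81 / 5 ≈ 16 to 162 / 5 ≈ 32 events per city if evenly spread). They should therefore accompany the overall figure rather than replace it.

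**Biomarkers and genetic markers.** Take effect sizes and p-values from data not used for selection, or from a method valid after selection. Cross-fitting is one option; a held-out subset is another where events allow. A compulsory half split is not needed: with about 81 events it would leave about 40 per half.

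**Wording.** Use the word *confirm* only for results obtained in that way.

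**Cost.** Extra computation, a less favourable reported AUC and, where data are held out, wider biomarker intervals (about √2 ≈ 1.4 times for a half split). No new data are needed.
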